#### Twenty-four-hour fluid balance

The absolute value and the change from baseline will be analyzed for the 24-h fluid balance parameter by means of summary descriptive statistics at each time point through day 7. Twenty-four-hour fluid balance at a given timepoint will be determined as the difference, at the timepoint, between the complete amount of fluid supplied to the patient over 24 h and the complete amount of fluid lost by the patient over the same period.

#### Hemodynamic parameters

The absolute value and the change from baseline will be analyzed for each hemodynamic parameter (i.e., mean arterial pressure, pulmonary blood volume (PBV), cardiac index and cardiac output) by means of summary descriptive statistics at each time point until the end of treatment.

#### Need for vasoactive drugs

The number and proportion of patients who required vasoactive drugs at any time through the end of treatment will be reported.
3.Baseline descriptive statistics

Patient demographics and baseline characteristics will be summarized on the ITT set, overall and by treatment cohort, and by means of summary descriptive statistics. A complete description of subject disposition will be provided, overall and by treatment cohort specifying the number of randomized subjects, number of subjects at each visit, and completed and discontinued subjects and the reason for the discontinuation. The analysis populations will be described and the reasons for excluding the subject from any analysis set will be provided with the number of protocol violators per each criterion. Medical history data will be presented by MedDRA System Organ Class and Preferred Term.
4.Treatments

The Safety Set will be used for the following analyses.

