Mild	200 mmHg < P_aO2_/F_iO2_ ≤ 300 mmHg with PEEP or CPAP ≥ 5 cm H_2_O ^b, c^
Moderate	100 mmHg < P_aO2_/F_iO2_ ≤ 200 mmHg with PEEP ≥ 5 cm H_2_O
Severe	P_aO2_/F_iO2_ ≤ 100 mmHg with PEEP ≥ 5 cm H_2_O

Abbreviations: *CPAP*, continuous positive airway pressure; *F*_*iO2*_, fraction of inspired oxygen; *P*_*aO2*_, partial pressure of arterial oxygen; *PEEP*, positive end-expiratory pressure

^a^ Chest radiograph or computed tomography scan

^b^ If altitude is higher than 1000 m, the correction factor should be calculated as follows: [P_aO2_/F_iO2_ × (barometric pressure/760)]

^c^ This may be delivered noninvasively in the mild acute respiratory distress syndrome group

Most cases of ARDS in adults are associated with pulmonary sepsis (46%) or non-pulmonary sepsis (33%). Risk factors include those causing direct lung injury (e.g., pneumonia, inhalation injury, pulmonary contusion) and those causing indirect lung injury (e.g., non-pulmonary sepsis, burns, polytrauma, transfusion-related acute lung injury) [4].

ARDS is an orphan condition. The in-hospital mortality rate for ARDS is estimated to be between 34 and 55% [5]. Risk factors for mortality include older age, multiorgan dysfunction and presence of pulmonary and non-pulmonary comorbidities. Most ARDS-related deaths are due to multiorgan failure. Refractory hypoxemia accounts for only 16 percent of ARDS-related deaths [6].

Treatment of ARDS is supportive, including mechanical ventilation, prevention of stress ulcers and venous thromboembolism, nutritional support and treatment of the underlying disease. Pharmacologic options for the treatment of ARDS are limited. The use of corticosteroids is controversial; randomized controlled trials and cohort studies tend to support the early use of corticosteroids for decreasing the number of days on a ventilator; however, no consistent mortality benefit has been shown with this therapy [7, 8]. No targeted pharmacological treatment of patients with pulmonary permeability edema in ARDS is currently available, and therefore, new therapeutic approaches are warranted.

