##### Informed consent

Male or female ≥ 18 years of agePatient has been admitted to an ICU, is mechanically ventilated and stable in this condition for at least 8 h.Moderate-to-severe ARDS diagnosis as defined by the Berlin definition:
Onset of ARDS within 1 week of a known clinical insult or new or worsening respiratory symptoms.Bilateral opacities not fully explained by effusions, lobar/lung collapse, or nodules.Respiratory failure not fully explained by cardiac failure or fluid overload (origin of edema).PaO2/FiO2 ≤ 200 mm Hg with Positive End-Expiratory Pressure (PEEP) ≥ 5 cm H_2_O.
4.Verified ARDS diagnosis (moderate or severe according to Berlin definition) not older than 48 h.5.Extravascular lung water index (EVLWI) ≥ 10 ml/kg PBW as assessed with a validated bedside measurement (single indicator transpulmonary thermodilution measurement, such as with PiCCO® from Pulsion or VolumeView from Edwards).6.Patient who meets criteria for extensive hemodynamic monitoring as per international intensive care medicine standards.

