#### Exclusion criteria

Patients must meet none of the exclusion criteria listed below.
History of clinically relevant allergies or idiosyncrasies to solnatide.Known use of any other investigational or non-registered drug within 30 days or within 5 half-lives of these drugs prior to study enrolment, whichever is longer. No exceptions are allowed in this study.Severe state of septic shock with a mean arterial pressure (MAP) ≤ 65 mmHg and a serum lactate level > 4 mmol/L (36 mg/dl) despite adequate volume resuscitation.An underlying clinical condition that, in the opinion of the investigator, would make it very unlikely for the patient to be successfully weaned from ventilation due to severe underlying diseases (e.g., severe malnutrition, severe neurological diseases, pulmonary fibrosis, or COPD).Extracorporeal membrane oxygenation, high-frequency oscillatory ventilation or any form of extracorporeal lung support. In no way are patients to be denied or delayed these procedures to avoid exclusion from the study.Neutrophil count < 0.3 × 10^9^/L.Cancer treatment (chemotherapy or biological) or therapy with other immunosuppressive agents for organ transplantation within 2 weeks.Cachexia (BMI < 18.5 kg/m^2^).Unequivocal cases of cardiogenic pulmonary edema (if differential diagnosis based on an ARDS triggering condition and clinical replicability is not possible, echocardiography may be indicated).Severe skin burns involving more than 15% of body surface.Subjects who are extremely unlikely to survive more than 48 h due to the acute conditions of the patient in the opinion of the investigator.Subjects transferred from a hospital not participating in this study who are already planned to be re- transferred during the observation period.Subjects who are not expected to survive the next month because of an underlying uncorrectable medical condition or a do not resuscitate order.Women known to be pregnant, women who are lactating, women with a positive or indeterminate pregnancy test, on screening, and males of reproductive potential and women of childbearing potential who are not willing to use highly effective methods of birth control/contraception for a duration defined in the patient’s Informed Consent Form.After randomization, drop-out of a participant is not envisaged by the protocol except for withdrawal of consent by the participant or his/her legal representative, discontinuation of the treatment (e.g., due to toxicity, or death of the patient during the treatment course).

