No multiplicity adjustment for multiple comparison will be applied, given that statistical comparison will be performed only between the highest solnatide dose cohort and the placebo cohort. A statistical comparison between lower dose(s) and placebo will be performed only in case of statistical significance of the comparison between the highest solnatide dose cohort and the placebo cohort.

#### Days of hospitalization through day 28

Length of hospital stay (in days) is defined as the difference between the discharge date and the randomization date. Patients still in the hospital at day 28 or who die during hospitalization will be censored at day 28. Days of outpatient hospitalization will not be included. Summary descriptive statistics will be provided for the number of days of hospitalization.

#### Days of stay at ICU through day 28

Length of stay at ICU (in days) is defined as the number of calendar days a patient was in the ICU. Patients still in the ICU at day 28 or who die during the stay at ICU will be censored at day 28. Summary descriptive statistics will be provided for the number of days of stay at the ICU.
2.Safety analyses

Safety analyses will be conducted on the Safety Set and will be reported by actual treatment cohort. No methodology for missing data handling will be applied for safety parameters.

#### Drug-related adverse events through day 14

The incidence of treatment-emergent drug-related AEs through day 14 after randomization, both in terms of number of events and in terms of patients with at least one event, will be tabulated by MedDRA System Organ Class (SOC) and Preferred Term (PT).

#### All adverse events through day 28

According to the onset date of the event, AEs will be defined as follows:
Treatment-emergent AEs are those events with an onset date after treatment initiation;Non-treatment-emergent AEs are those events with an onset date between screening and treatment initiation.

Non-treatment-emergent adverse events will be listed only. The incidence of treatment-emergent adverse events (TEAE) will be tabulated by MedDRA System Organ Class (SOC) and Preferred Term (PT). The incidence of TEAEs will also be summarized by system organ class, preferred term, and severity (based on investigator’s judgment).

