#### Concomitant treatments

Concomitant medications or procedures taken concurrently with the study treatment will be listed and summarized by WHO Anatomical Therapeutic Chemical (ATC) Class and Preferred Term. These summaries will include medications starting on or after the start of study treatment, or medications starting prior to the start of study treatment and continuing after the start of study treatment. Prior medications starting and ending prior to the start of study treatment will be listed only.

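### The vasoactive-drug safety measure counts any use and does not separate patients already on these drugs at first dose, so it mixes pre-existing with new need and cannot show escalation

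*Protocol article*

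**What the plan says.** The Outcomes section of the protocol article lists need for vasoactive drugs among ten safety parameters and defines no formal primary or secondary outcome. The statistical section headed "Need for vasoactive drugs" gives the rule in one sentence: "The number and proportion of patients who required vasoactive drugs at any time through the end of treatment will be reported". It names no start of the window, no baseline status, and no category for new starts or rising requirement.

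On who can enter, the exclusion criteria remove a "Severe state of septic shock with a mean arterial pressure (MAP) ≤ 65 mmHg and a serum lactate level > 4 mmol/L" that persists despite adequate volume resuscitation. Both the pressure and the lactate condition must be met, and use of a vasoactive drug is not itself an exclusion. One inclusion criterion asks for a "Patient who meets criteria for extensive hemodynamic monitoring as per international intensive care medicine standards".

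Other safety outputs have a reference point. Under All adverse events, "Treatment-emergent AEs are those events with an onset date after treatment initiation". Under Hemodynamic parameters, "The absolute value and the change from baseline will be analyzed for each hemodynamic parameter". Vital signs, laboratory values and fluid balance are also compared with baseline. The Concomitant treatments summary includes new starts together with "medications starting prior to the start of study treatment and continuing after the start of study treatment".

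**The concern.** Circulatory harm from the study drug would show as a patient starting a vasoactive drug after the first dose, restarting one, or needing more of it. The planned count captures only the first of these. It also adds those patients to others who were on the drugs before any study treatment and whose status cannot change. The trial's main objective is safety, and each dose group has 20 patients, so a diluted signal soon amounts to only two or three patients. The summary of concomitant medication does not make the separation either, because it pools carried-over drugs with new ones.

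**Working it through.** **The plan's own figures.** The article states no rate, sample size or power for this measure, so there is no figure to reproduce. Its only power statement concerns the change in EVLWI (20 per group, difference 3.2 ml/kg, SD 3.5, two-sided 0.05). That reproduces at 80.4% with a two-sample t-test and has no bearing here.

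**Inputs from the document.** There are 20 patients per dose and 35 on placebo in total (Trial design; Sample size). The allocation section gives 4:1 rather than 1:1 for the third step, which would reduce the placebo number. That is a separate matter: the dilution below does not depend on it, only the power figures do.

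**Assumed inputs, not in the document.** b is the share on vasoactive drugs at first dose, the same in both groups. h is the risk of a new start among the rest, set at 20% on placebo and 50% on one dose.

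**Formulas.**
- Any-use proportion = b + (1 − b)h.
- Apparent difference = (1 − b)(0.50 − 0.20).
- Share of counted placebo patients who were already users = b / [b + 0.20(1 − b)].

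Example at b = 0.5: placebo 0.5 + 0.5 × 0.20 = 0.60; dose 0.5 + 0.5 × 0.50 = 0.75; difference 0.15; share 0.50/0.60 = 0.83.

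Power is for a two-sided Fisher test at 0.05. It is used only as a yardstick, since the plan has no test for this measure. The last two columns restrict to patients not on the drugs at first dose, with group sizes rounded.

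| b | Any use, placebo | Any use, dose | Difference (points) | Already users, share of placebo count | Power, any use, 20 v 35 | Non-users, dose v placebo | Power, new starts |
|---|---|---|---|---|---|---|---|
| 0 | 20% | 50% | 30 | 0% | 59% | 20 v 35 | 59% |
| 0.3 | 44% | 65% | 21 | 68% | 29% | 14 v 24 | 40% |
| 0.5 | 60% | 75% | 15 | 83% | 17% | 10 v 18 | 30% |
| 0.7 | 76% | 85% | 9 | 92% | 8% | 6 v 10 | 20% |
| 0.8 | 84% | 90% | 6 | 95% | 5% | 4 v 7 | 9% |

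In a dose group of 20, the excess is 0.30 × 20 = 6 patients with no baseline use. It is 4.2, 3.0 and 1.8 patients at b = 0.3, 0.5 and 0.7.

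**When a ceiling is near.** Setting placebo any-use to 85% gives b + 0.20(1 − b) = 0.85, so b = 0.65/0.80 = 0.81.

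**Chance imbalance in b.** At b = 0.5, the standard deviation of the difference in baseline use is √(0.25/20 + 0.25/10) = 19 points in step 1 (20 v 10), √(0.25/20 + 0.25/5) = 25 points in step 2 (20 v 5), and √(0.25/20 + 0.25/35) = 14 points for 20 v 35. An imbalance enters the any-use difference multiplied by 1 − h, here 0.80, giving about 15, 20 and 11 points. Without use at first dose in the table, a reader cannot tell such an imbalance from a drug effect.

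**Escalation.** No arithmetic is needed. A patient counted at first dose contributes the same value whether the requirement falls to zero or rises, so the measure carries no information on escalation in the share b.

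**The case against.** The strongest case against is that this is one descriptive row among ten safety parameters, with no test and no decision threshold attached. Circulatory signals have other routes: adverse events split at treatment start, change in SOFA to day 7, change in mean arterial pressure and cardiac index, and the concomitant-medication listings. Where the article names what the DSMB considers in its final safety statement, vasoactive use is not mentioned. Small unstratified groups make every parameter noisy, and comparison with placebo is randomised within each step. An analysis plan that is not shown may split the row by baseline status. The gain in detection is also small: at b = 0.5, power rises only from 17% to 30%.

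Most of this stands, and it limits the weight of the point. It does not remove it. The article defers censoring rules, extra imputation and subgroups to the analysis plan, but here it states a complete rule and defers nothing. Pressure and cardiac index can look stable because vasoactive support is rising, so they are not a full substitute.

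A reader might go further and infer that the measure sits near its ceiling and mostly reports shock present at entry. The document does not support that as fact. It gives no rate of vasoactive use at entry. Its 46% and 33% figures are sepsis associations for ARDS in general, not vasoactive-drug rates in this trial. The monitoring criterion does not say that the patient is in shock, and the exclusion removes the severest septic shock, which lowers b.

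**Conclusion.** The point holds as a matter of definition: the stated count mixes pre-existing with new need and cannot show escalation, because eligibility admits patients already on these drugs and no split is specified. Its size depends on b, which the document does not give. Under the assumed 20% versus 50% new-start risks, 30 points become 21, 15 or 9 at b = 0.3, 0.5 or 0.7. A ceiling needs b of about 0.8 or more, which nothing in the document establishes. That the count is mostly baseline users is likewise conditional: it requires b > h/(1 + h), which is 0.20/1.20 = 0.17 at the assumed placebo risk, and the document gives neither b nor h. Nor is the signal lost to the trial, since other outputs may carry it. The flaw is one poorly defined summary row, and it rates as a cheap improvement.

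**What to change.** Under Need for vasoactive drugs, report by treatment cohort:

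- (a) the number and proportion on vasoactive drugs at first dose;
- (b) new starts after first dose, among patients not on them at first dose;
- (c) restart or increase, among patients on them at first dose;
- (d) the any-use count as now, as a descriptive line, with the start of its window stated.

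Item (b) needs only the medication start dates that the Concomitant treatments section already uses. For (c), use concomitant-medication dates and, where dose is not recorded, the cardiovascular component of SOFA to day 7. This assumes that the component is stored and not only the total score.

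The cost is a few extra table rows and no change to trial conduct, provided those records hold what is needed. The downside is small denominators, for example about 10 v 18 in (b) if b = 0.5, and only a modest gain in the ability to detect a difference. The main benefit is that the figure becomes interpretable.

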#### Investigational treatment

Duration of exposure to study treatment, defined as the time (days) elapsed from the date of the first treatment administration to the date of the last treatment administration and number of administrations will be summarized. Cumulative dose (mg), defined as the total dose given during treatment exposure, will be summarized. The number of patients with dose interruptions/permanent discontinuation will be presented along with the reasons for the dose interruptions/discontinuation.

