#### Placebo

This is commercially available 0.9% saline solution in vials.

Patients will receive 5 ml of the study drug containing 5 mg, 60 mg, or 125 mg solnatide or 0.9% saline according to treatment allocation via endotracheal nebulization every 12 h for a maximum of 7 days using an Aeroneb Solo nebulizer.

Reconstituted solnatide as well as placebo solution (saline) will be supplied in a closed and labelled syringe to study personnel authorized for administration. Both solutions are clear and colorless, and thus indistinguishable in appearance.

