#### Dosing and administration

In this dose ascending study, 3 groups of patients (one for each dosage) will be randomized to treatment with either solnatide or placebo. The three doses administered in this study are 5 mg, 60 mg, and 125 mg and escalation from one dose to the next will occur only once a DSMB has carefully reviewed the safety data emerging from the last treatment group and has approved the administration of the next highest dosage. The highest dosage used in this study has already been tested and has proved to be safe in a Phase I and two Phase II trials and no dose-limiting effects are expected.

Patients will be treated with solnatide or placebo twice a day for 7 days via endotracheal inhalation. Inhalations should be scheduled around 08:00 a.m. (± 30 min) and 08:00 p.m. (± 30 min). The 12-h sequence should be followed as closely as possible. If applicable to the routine of the ICU, inhalation can be shifted to a later time until 10:00 a.m. (± 30 min) and 10:00 p.m. (± 30 min), respectively, at the latest.

To enable endotracheal inhalation, reconstituted solnatide in water for injection is converted into an inhalable aerosol by the Aeroneb Solo medicinal device. This device is a product of Aerogen, Galway, Ireland, and is a commercially available liquid nebulizer. The Aerogen Solo nebulizer has been approved in the European Community by CE-marking based on requirements of Annex II, Section 3.2. of Directive 93/42/EEC.

The nebulizer unit holds up to 6 ml of liquid medication. The nebulizer unit is clear to allow visual monitoring of medication levels and aerosolization. When the nebulizer unit is connected to the ventilator circuit, the silicon plug can be opened and closed in between doses without causing loss of circuit pressure.

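### Duration of exposure is counted from first to last administration date, so a full 7-day course started in the morning scores 6 days and treatment on a single date scores 0

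*Protocol article*

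**What the plan says.** Under Investigational treatment, the protocol article defines duration of exposure as "the time (days) elapsed from the date of the first treatment administration to the date of the last treatment administration". The same sentence also has the number of administrations summarized. The next one adds: "Cumulative dose (mg), defined as the total dose given during treatment exposure, will be summarized". Interruptions and permanent discontinuations are to be shown with their reasons. All of this is done on the Safety Set and is descriptive.

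The schedule to which the definition applies is given in two places. Dosing and administration says: "Patients will be treated with solnatide or placebo twice a day for 7 days via endotracheal inhalation". The Placebo subsection, which covers both arms, gives the interval and the cap: "every 12 h for a maximum of 7 days using an Aeroneb Solo nebulizer". The two daily slots are about 08:00 and 20:00, and may move to 10:00 and 22:00 at the latest. The text shown does not say in which slot the first dose is given. The schedule of activities is a figure that is not shown.

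**The concern.** A duration-of-exposure variable should return the planned length when the planned course is completed, and something above zero for anyone who was treated. A plain first-to-last date count does neither. It leaves out the opening day and gives no credit for the interval after the last dose.

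The trial's main objective is the safety of 7 days of inhalation, so the exposure table is where a reader looks to see how much treatment lies behind the adverse-event counts. As defined, it could show completers at 6 days beside 14 twice-daily administrations. It could also show patients who stopped or died on the first date as treated for 0 days. Each active cohort is planned at 20 patients, so a one-day shift in most of them would be visible in the cohort mean.

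**Working it through.** **Inputs, all from the protocol article**

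- Rule: days from first administration date to last administration date (Investigational treatment).
- Course: 2 per day × 7 days = 14 administrations (Dosing and administration).
- Interval: 12 h (Placebo).
- Slots: 08:00 and 20:00. Using 10:00 and 22:00 gives the same results.
- Slot of the first dose: not stated, so both cases are computed.

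**Reference value.** The planned length is 7 days. Crediting each dose with its 12-hour interval gives 14 × 12 h = 168 h, and 168/24 = 7.0 days.

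**Rule as written.** The time from first to last of 14 doses is 13 × 12 h = 156 h = 6.5 days.

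- Morning start: day 1 at 08:00 + 156 h = day 7 at 20:00. Date difference 7 − 1 = 6 days, against 7 planned (−1/7 = −14%).
- Evening start: day 1 at 20:00 + 156 h = day 8 at 08:00. Date difference 8 − 1 = 7 days.

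| Doses given | First slot | Date difference (as written) | Exact elapsed days | Date difference + 1 | (Elapsed + 12 h)/24 h |
|---|---|---|---|---|---|
| 14 | morning | 6 | 6.5 | 7 | 7.0 |
| 14 | evening | 7 | 6.5 | 8 | 7.0 |
| 13 | morning | 6 | 6.0 | 7 | 6.5 |
| 13 | evening | 6 | 6.0 | 7 | 6.5 |
| 2 | morning | 0 | 0.5 | 1 | 1.0 |
| 2 | evening | 1 | 0.5 | 2 | 1.0 |
| 1 | either | 0 | 0 | 1 | 0.5 |

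**Generous reading.** If elapsed time means exact clock time, a full course gives 6.5 days from either start and a single dose still gives 0. This removes the start-time difference, but the result is still not 7 days, and a patient given one dose still has no exposure.

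**Range for completers.** If a share p of 14-dose completers start in the evening, their mean under the written rule is 6(1 − p) + 7p = 6 + p. It is 6.0 at p = 0, 6.5 at p = 0.5 and 7.0 at p = 1, for identical treatment. The value of p is an assumption; the documents give nothing on it.

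**Precision of the date-time fix.** Slots may shift by up to 2 h. A first dose at 08:00 on day 1 and a last at 22:00 on day 7 are 158 h apart, and (158 + 12)/24 = 7.08. A first dose at 10:00 and a last at 20:00 are 154 h apart, and (154 + 12)/24 = 6.92. A full course therefore gives about 7.0 rather than exactly 7.0.

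**The case against.** The strongest reply is that the exposure section already carries what a reader needs. A completer will show 14 administrations, and a patient treated on one date will show one or two, with a cumulative dose above zero if on solnatide. Adverse events are tabulated as events and as patients with an event, not per day of exposure. The review items listed for the DSMB's final session are mortality, adverse events, laboratory data and ECGs, not treatment duration. All of this stands, and it limits the point to a small one. A reader might infer that completers will look undertreated or that the safety conclusions are biased. The documents do not support that.

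A second reply is that the definition is prose, that the article states subtraction outright elsewhere (time to extubation, hospital stay), and that adding a day is a convention commonly left to the analysis plan. This stands only in part. The analysis plan, not shown, could add it. But the article does state a rule, and neither the date reading nor the clock-time reading of that rule returns 7 days for a full morning-start course or a positive value for a single dose.

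A third reply concerns the start-time effect. A reader might infer that identical courses will certainly score differently. That needs an evening first dose, which the text shown neither provides for nor rules out. If treatment also stops at the end of calendar day 7, an evening starter has 13 doses and scores 6, the same as a morning starter with 14. The effect can therefore only be stated conditionally.

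Nor is every morning starter's elapsed time understated. Three doses from a morning start span exactly 1.0 day, and the rule gives 1. The shortfall there appears only when 12 h are credited to the last dose.

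**Conclusion.** The point holds and is minor. Read literally, the definition gives 6 days for a full 14-dose course begun in the morning, and 0 days for a patient treated on one calendar date only. Neither result needs any assumption beyond the stated 12-hourly schedule and, for the zero, that a treated patient belongs to the Safety Set, which the article uses but does not define. The 7-day score for the same 14 doses is conditional on an evening first dose being possible.

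The error is at most one day per uninterrupted course when measured against 12 h per dose. It is confined to one descriptive summary with clear companion measures beside it. No hypothesis test, dose-escalation rule or adverse-event rate depends on it.

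**What to change.** Replace the definition, in the protocol or in the analysis plan with a note that it supersedes the protocol wording:

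- **If administration times are captured:** duration = (last administration date-time − first administration date-time + 12 h)/24 h. This gives about 7.0 days for a full course from either slot, 1.0 for two doses 12 h apart and 0.5 for a single dose. The article gives scheduled times but does not say that actual times are recorded, so this must be confirmed first.
- **If only dates are captured:** duration = last date − first date + 1, labelled as calendar days on treatment. This removes the zero and gives 7 for a morning-start course. It does not remove dependence on the start slot: an evening-start 14-dose course counts 8 calendar days, and a footnote should say so. The article already counts ICU stay in calendar days, so the label fits its usage.

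Dividing the number of administrations by two is not a substitute. It measures doses rather than duration once doses are missed, and it only rescales a summary already planned.

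The cost is one line of text and one line of programming, with no effect on conduct, dosing or sample size.
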